#### Intervention Fidelity

Fidelity measures will be employed to ensure consistent delivery of the ME-WE intervention across facilitators and locations. First, it is a requirement that all facilitators have experience working with groups and young people. Second, role-playing exercises will be applied in the training of facilitators to have them practice and increase their confidence in the implementation of the intervention. Third, a standardized, detailed intervention manual will be available to facilitators. Fourth, following the delivery of each session, cofacilitators will complete a semistructured questionnaire to evaluate adherence to the intervention manual, skills in creating a positive group environment and participants’ engagement. Finally, facilitators will receive monthly supervision from a mental health professional trained in the DNA-V to ensure intervention fidelity and to offer supplemental supervisory support as needed.

### 2.4. Control

Participants of clusters allocated to the waitlist control group will not receive an intervention. They will perform ice-breaker and team building activities during 3 face-to-face meetings organized to correspond with the three assessment points with the aim of collecting outcome measures data. They will be offered to receive the ME-WE intervention after the experimental group has completed all the assessments (i.e., after the 3 months follow-up).

### 2.5. Outcome Measures

Demographic (gender, age, country of birth, nationality, migration background, place of living, living conditions and family composition) and caregiving information (number and age of people cared for, type of relationship with the care recipient, nature of the illness or health condition of the care recipient and time since caregiving started) will be collected at baseline (T0). Primary and secondary outcomes and control variables will be collected at baseline (T0), post-intervention (T1) and 3 months post-intervention (T2). T0, T1 and T2 assessments in the ME-WE intervention group will be performed at the beginning of session 1, at the end of session 7 and at the beginning of session 8, respectively. Primary outcome variables will include psychological flexibility, mindfulness skills, resilience, subjective mental and physical health, general and caring-related quality of life, impact of caring and social support. Secondary outcome variables will be self-reported school/training/work experience, performance and attendance. The following variables will be used as control variables: caring activities, overall amount of caring, likes and dislikes of caring, formal support received and caring-related perceived social support. Both quantitative and qualitative data will be collected using a questionnaire available in both web-based and paper-and pencil versions. All selected standardized self-report measures were specifically developed and/or tested for use with adolescents. Measures not available in the local languages of participating countries have been translated after permission from the authors. The committee translation method was used [71]. Specifically, in non-English countries, two independent researchers fluent in English independently translated each measure from English into their local language, and then met to discuss eventual discrepancies and reach consensus on an integrated version. English questionnaires were used for participants in the United Kingdom. Ad-hoc developed items were formulated in English and then translated using the same procedure used for standardized tools. Participants in the intervention group will complete a post-intervention self-assessment tool at T1 and T2. Process evaluation outcomes will include feasibility, acceptability and fidelity indicators.

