## 2. Original Study Protocol Methods

### 2.1. Study Design

This study is a two-armed, parallel group cluster RCT that will be executed in six European countries (Italy, Slovenia, Sweden, Switzerland, the Netherlands and United Kingdom). Cluster randomization is used to minimize contamination between intervention and control arms [61]. Indeed, if randomization were performed at the individual participant level, there would be a risk for exchange of information between AYCs within the same cluster. Clusters will consist of AYCs attending the same school (in Slovenia, Sweden and Switzerland) or living in the same geographical area (i.e., neighborhood or post-code area) (in Italy, the Netherlands and the United Kingdom). Clusters will be randomly assigned to either the ME-WE intervention or the waitlist control (1:1 allocation ratio), so that all eligible participants from the same school or geographical area are in the same study arm. Randomization will be conducted by a research member who is neither involved in the recruitment nor in the intervention delivery, using an online number generator. To achieve a certain degree of blinding, both schools and community-based service organizations (for geographical area clusters) and participating AYCs will be informed that the study aims to investigate the effects of different support strategies on AYCs’ well-being. They will not be told which condition they have been allocated to, nor will they be offered detailed information about the respective other trial arm during the study. Outcomes will be measured at the individual level. Both the ME-WE intervention and the waitlist control group will be assessed at baseline (T0), immediately post-intervention for the ME-WE intervention group or after 7 weeks for the waitlist control group (T1), and at a 3 months follow-up (T2). Participant-reported outcome measures will be used. Trial data analysts will be blinded to group allocation. After the 3 months follow-up the waitlist control group will receive the same program as the intervention group. The consolidated standard of reporting trials (CONSORT) 2010 statement extended to cluster trials is followed in this study [62]. The research flow diagram is presented in Figure 1. This protocol is based on the SPIRIT (standard protocol items: recommendations for interventional trials) guidelines [63] and has been registered at clinicaltrials.gov (accessed on 22 September 2019, trial registration number: NCT04114864).

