#### 2.5.5. Process Evaluation Outcomes

A number of process evaluation outcomes will be monitored, following Linnan and Steckler [111]. Indicators of feasibility will include the proportion of eligible AYCs who will participate in the trial, the proportion of AYCs in the intervention group who will attend ≥70% of intervention sessions, and the proportion of AYCs who will be lost to follow-up. These feasibility indicators will be assessed using attendance lists (for the intervention group) and completion of assessment questionnaires (for the control group). To assess intervention acceptability, 5 open-ended questions included in the post-intervention self-assessment [110] will ask AYCs for their perceptions about the support they received from the intervention, what changed for them and for their caring role because of participating in the intervention and what they did not like about the intervention. For fidelity, a semistructured questionnaire will be completed by cofacilitators following each intervention session to evaluate whether the ME-WE intervention was delivered as planned.

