### 2.8. Statistical Analyses

Statistical analyses will be performed at both national and cross-national levels. Data will be analyzed using intention-to-treat principles [119] and adjusted for cluster effect [62]. Baseline characteristics will be preliminarily compared to check equivalence between study groups using analysis of variance (ANOVA) and *χ*^2^ tests. To answer primary and secondary research questions, differences in primary and secondary outcomes between the study arms from T0 through T1 and T2 will be tested using linear mixed effect models. These analyses will be based on individual participant-level data, allowing for clustering between AYCs within the same school or geographical area [62,120]. Models will include the fixed effects of study arm, country and delivery approach, time and their interaction effects. The cluster will be considered as a random effect. Models will be adjusted for characteristics that are unbalanced between study arms and significantly associated with the outcome measures. In case of violations of assumptions underlying planned analyses (e.g., equal variance and normal distribution of residuals) appropriate mathematical transformations of raw scores (e.g., logarithmic scale) or robust estimation methods will be applied [121]. Interpretation of results will be based on both statistical significance (*p* < 0.05, two-tailed) and measures of effect size [122]. We will also summarize post-intervention self-assessment and process evaluation measures. Analysis of qualitative data in national languages (for control variables likes and dislikes about caring and for intervention acceptability) will be performed using content analysis [123].

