### 3.4. Outcome Measures Amendments

Assessments will be performed solely online, using the web-based version of the study questionnaires. Additional COVID-related measures will be included. Specifically, the perceived impact of the COVID-19 pandemic on everyday life and perceived mental health [128] will be assessed at all assessment points in both study groups. At T1 and T2, AYCs in the intervention group will be also asked for their experiences with participating in the ME-WE intervention during the pandemic and their evaluation of the online delivery mode.

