## 4. Trial Status

The recruitment of participants started in May 2019. Randomization began in September 2019, and the first baseline assessment was completed on 24 October 2019. Before COVID-19-related amendments (April 2020), a total of 98 AYCs was recruited. The trial is currently ongoing. Preliminary data available from Italy (*n* = 22, October 2019–March 2020) indicated feasibility of the ME-WE trial and acceptability of the ME-WE intervention. The proportion of eligible AYCs (screened between May and September 2019) who participated in the trial was 84%. Seventy-three percent of AYCs in the intervention group attended at least 70% of intervention sessions. Twenty-eight percent of all participants were lost to follow-up. Responses of AYCs in the intervention group to the post intervention self-assessment indicated that participants had a clearer vision of their thoughts, took better care of themselves and were generally satisfied with and enjoyed the intervention.

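### Intervention-arm T1 and T2 are scheduled inside sessions 7 and 8, so absentees may go unmeasured and missing outcomes are tied to adherence in one arm only

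*Protocol article*

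**What the plan says.** Section 2.5 (Outcome Measures) fixes the intervention arm's T1 and T2 "at the end of session 7 and at the beginning of session 8, respectively". Session 8 is the follow-up meeting three months after the programme ends (Section 2.3). Section 2.1 describes T1 as "immediately post-intervention for the ME-WE intervention group or after 7 weeks for the waitlist control group (T1".

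Section 2.4 (Control) assesses the waitlist arm at "3 face-to-face meetings organized to correspond with the three assessment points with the aim of collecting outcome measures data".

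Section 2.5.5 lists three feasibility indicators: participation among eligible adolescents, attendance at 70% or more of sessions, and loss to follow-up. It then states: "These feasibility indicators will be assessed using attendance lists (for the intervention group) and completion of assessment questionnaires (for the control group".

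Section 2.8 promises: "Data will be analyzed using intention-to-treat principles". Outcomes in the cluster-randomised countries "will be tested using linear mixed effect models". Section 3.6 uses mixed ANOVA for Sweden and Switzerland.

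Among the COVID-19 amendments, Section 3.4 states: "Assessments will be performed solely online, using the web-based version of the study questionnaires". It changes the mode and not the timing, and the opening of Section 3 keeps Section 2 in force wherever no change is specified.

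Section 4 reports preliminary Italian data (n = 22): "Seventy-three percent of AYCs in the intervention group attended at least 70% of intervention sessions", and 28% of all participants lost to follow-up.

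**The concern.** An intention-to-treat comparison needs outcomes from everyone randomised, including those who stop the programme. Here the planned occasion for measurement in one arm is a treatment session. To be measured at T1, an intervention participant has to be present at the end of the last of seven weekly two-hour sessions. A control has to come to a meeting that exists for measurement.

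The wording on loss to follow-up points the same way. If attendance lists supply that indicator in the intervention arm, an adolescent who leaves the programme and one who is lost to assessment are not told apart. In the control arm they are judged by the questionnaire itself.

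Section 5 expects that carers may find a seven-week programme hard to sustain, so stopping is plausibly related to caring burden and through it to the outcomes. If those who stop go unmeasured, the estimate drifts from the effect in all randomised toward the effect in attenders. T1 and T2 values that were never collected cannot be recovered at analysis.

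**Working it through.** **1. The passages side by side**

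| | Intervention arm | Control arm |
|---|---|---|
| Occasion of T1 and T2 | end of session 7, start of session 8 (2.5) | meetings held for data collection (2.4) |
| Source for feasibility indicators, including loss to follow-up | attendance lists (2.5.5) | questionnaire completion (2.5.5) |
| Changed by amendment? | mode only (3.4) | mode only (3.4) |

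The article describes no route for assessing someone absent from session 7 or 8. Section 5 offers general communication and reminders.

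**2. What the analysis can recover.** A participant with neither T1 nor T2 contributes only T0. A likelihood-based mixed model can use T0 if missingness depends only on observed data. Mixed ANOVA in its usual form uses complete cases, so in Sweden and Switzerland T0 may be lost too.

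**3. The plan's own figures.** Attrition allowance (3.5): 24 × 1.20 = 28.8, rounded to 29 per group, 58 in total, as stated. This allows for how many are lost and says nothing about who. Target effect (2.7): f = 0.25, so d = 2 × 0.25 = 0.5 for two groups. Italian low attendance (4): 100% − 73% = 27%.

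**4. Illustration of size.** Assume a share p of the intervention arm is unmeasured, attendance follows a normal latent variable, and its correlation with the T1 score is r. The observed intervention mean then shifts by r × φ(z_p)/(1 − p), where the second factor is 0.453 at p = 0.27 and 0.350 at p = 0.20. All values of r are assumed.

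| p | r = 0.2 | r = 0.3 | r = 0.5 |
|---|---|---|---|
| 0.27 | 0.09 SD | 0.14 SD | 0.23 SD |
| 0.20 | 0.07 SD | 0.10 SD | 0.17 SD |

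**5. After baseline adjustment.** These are raw shifts. If attendance also correlates 0.3 with T0, and T0 correlates 0.6 with T1 (both assumed), about 0.453 × (0.3 − 0.3 × 0.6) = 0.453 × 0.12 = 0.05 SD remains of the 0.14. If attendance were unrelated to T0, adjustment would remove nothing.

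**6. A second route.** Suppose attenders gain 0.50 SD, 27% stop and are unmeasured, and control loss is unrelated to outcome. If stoppers gain nothing, the effect in all randomised is 0.50 × 0.73 = 0.365, an overstatement of 0.50/0.365 = 1.37 times. If they gain half, it is 0.50 × (0.73 + 0.135) = 0.43, an overstatement of 1.16 times.

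**7. Whether 27% and 28% can serve as inputs**

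- The 27% is attendance below 70%, not absence at session 7 or 8. Someone who attends 5 of 7 sessions (71%) passes the threshold and may still miss session 7. A low attender may be present at it.
- It comes from 22 participants over both arms. If about 11 were in the intervention arm (assumed), 27% is three adolescents.
- The 28% is pooled. With equal arms (assumed), an intervention-arm loss of 27% would imply a control loss of 2 × 28 − 27 = 29%.
- 28% of 22 is 6.2, not a whole number, so the denominator is unclear.

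**The case against.** A reader might infer that non-adherers are not measured at all, that intention-to-treat is thereby lost, and that the result is inflated by 0.09 to 0.23 SD. The documents do not support that.

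- No passage says absentees receive no questionnaire. A web version existed from the outset and is now the only mode, and chasing absentees is operational detail that a fuller protocol may cover.
- Someone who stops before session 7 is not barred from returning three months later for session 8, so T2 need not be missing.
- Controls can also miss their meetings, for reasons related to outcome. The pooled 28% shows no difference in loss between arms.
- Section 2.5.5 names attendance and loss to follow-up as separate indicators, even though it gives both one source per arm.
- The SD shifts rest on assumed correlations and on a proxy percentage, and they leave out T0.
- Direction is not fixed. Adolescents may stop because caring demands rise or because they feel less need of help.

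All of this stands, and it limits what can be said about occurrence, size and direction. It does not remove the asymmetry, which is stated text and not an inference from silence: one arm is assessed within treatment and the other at data-collection meetings, with a different source for loss to follow-up in each.

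**Conclusion.** The point holds as a weakness in a stated procedure. It is not a demonstrated bias. Followed as written, and unchanged by the move to web questionnaires, the plan ties outcome ascertainment to adherence in the intervention arm only. Adolescents absent from session 7 or 8 may go unmeasured, and the intention-to-treat comparison may then be biased, probably but not certainly in favour of the intervention.

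The size cannot be derived from the documents. The 0.07 to 0.23 SD range is illustrative. It assumes that 20% or 27% are unmeasured, that the correlation is 0.2 to 0.5 and that controls show no matching shift. In the mixed model it is smaller to the extent that attendance is related to T0. The Italian figures show that incomplete attendance and loss on this scale occur. They do not show that loss differs between arms.

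**What to change.** - **Sections 2.5 and 3.4:** send the web questionnaire to every randomised participant in both arms at the scheduled T1 and T2 dates, with the same reminders, whether or not they attend the session or have stopped the programme.
- **Section 2.5.5:** define loss to follow-up by questionnaire completion in both arms, keep attendance lists for the attendance indicator, and record stopping the programme separately from withdrawing from assessment.

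The cost is protocol wording and automated links, since the questionnaire is already web-only. The downside is small: some questionnaires will be completed outside a session. The trial is described as ongoing, and the change helps only participants whose T1 or T2 is still to come, so it should be made promptly.

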#### 2.5.1. Primary Outcomes

Psychological flexibility will be assessed using the avoidance and fusion questionnaire for youth (AFQ-Y) [72] (8 items, 5-point scale ranging from not at all true to very true). The AFQ-Y has been developed based on the ACT model and validated for use with youth into several languages, including Italian [73], Dutch [74] and Swedish [75,76]. All versions showed adequate reliability and concurrent validity with measures of internalizing and externalizing symptoms [72,73,74,75,76]. Mindfulness skills will be measured with the child and adolescent mindfulness measure (CAMM) [77] (10 items, 5-point scale ranging from never true to always true). The original CAMM has been validated in a large sample of children and adolescents, showing a one-factor structure with adequate internal consistency and associations in the expected directions with a number of criterion measures (e.g., quality of life and internalizing and externalizing problems) [77]. The validated Italian [78,79,80] and Dutch [81] versions used in this study demonstrated sound reliability and construct validity. Both the AFQ-Y and CAMM showed sensitivity to change when used with children and adolescents receiving ACT- or mindfulness-based interventions, e.g., [57,82,83,84,85]. To assess resilience, the brief resilience scale (BRS) [86] (6 items, 5-point scale ranging from strongly disagree to strongly agree) will be applied. The original BRS showed evidence of validity and reliability as a one-factor measure of the ability to recover from stress and has already been used in research with AYCs [87]. The Dutch [88] and German [89] adaptations used in this study demonstrated adequate reliability, meaningful associations with mental health symptoms and confirmed the BRS original structure. The Warwick Edinburgh mental well-being scale (WEMWBS) [90] (14 items, 5-point scale ranging from none of the time to all of the time) will be used for measuring subjective mental health. The original WEMWBS was developed in the United Kingdom and showed sound psychometric proprieties including internal consistency and evidence of validity based on content, internal structure and relations with other mental health and well-being scales [90]. This widely used measure has been tested for use with adolescents [91] and proved valid and reliable in its Italian [92], Dutch [93], Slovenian [94], Swedish (7-item WEMWBS) [95] and German [96] adaptations. Subjective physical health will be assessed with the health behavior in school-aged children symptom checklist (HBSC-SCL) [97] (8 items, 5-point scale ranging from about every day to rarely or never). The HBSC-SCL has been developed within the HBSC study, a World Health Organization collaborative cross-national study of adolescent health and well-being that includes fifty countries and regions across Europe and North America, including the six countries of the present study [98]. Validation studies on the HBSC-SCL indicate that it measures two dimensions of subjective health complaints (i.e., psychological and somatic) with adequate internal consistency and test–retest reliability, and content, convergent and discriminant validity [99,100]. For general quality of life, the KIDSCREEN-10 [101] (10 items, 5-point scale ranging from not at all/never to extremely/always) will be employed, with an additional item on subjective general health (5-point scale ranging from excellent to poor) and one multiple-choice ad-hoc question on currently experiencing health-related issues (i.e., mental health problems, physical disabilities, learning difficulties or other). The KIDSCREEN-10 was developed from the 27-item KIDSCREEN to obtain a Rasch-scaled single score of quality of life for children and adolescents. It was validated in a large sample of youth across thirteen European countries, including Italy, Netherlands, Sweden, Switzerland and United Kingdom, showing adequate reliability and construct and criterion validity [102]. The KIDSCREEN-10 has been adopted in the HBSC study and has been used in research on AYCs [13,103]. The translations used in this study were taken from [104]. Caring-related quality of life will be assessed using 3 dichotomous (yes/no) ad-hoc questions regarding thoughts about hurting oneself and others, and being bullied, teased or made fun of, and one multiple-choice ad-hoc question on experienced health-related issues (i.e., mental health problems, physical health problems or other) because of the caring role. Perceived cognitive and emotional impact of caring will be assessed using the positive and negative outcomes of caring (PANOC) [105] (20 items, 3-point scale ranging from never to a lot of the time). The PANOC was specifically developed for and validated in YCs in the United Kingdom. It consists of two 10-item subscales (positive and negative outcomes) with adequate internal consistency and expected associations with depressive symptoms [105]. A Swedish adaptation has been used in previous studies, showing adequate internal consistency [6]. Finally, perceived social support will be measured using an adapted version of the brief social support questionnaire (SSQ-6) [106] that includes 3 items asking to indicate the number of support sources and one item asking for global satisfaction with received social support (6-point scale ranging from very dissatisfied to very satisfied), and one multiple-choice ad-hoc question on individuals (i.e., school staff, close family members and close friends) AYCs can count on if in need of support or help. The original SSQ-6 validation study indicated a two-factor structure (availability of and satisfaction with social support) with adequate reliability and expected relations with personality dimensions [106]. The Dutch adaptation showed adequate reliability [107]. The SSQ-6 has been previously used with adolescent populations [108] and with AYCs showing good reliability and meaningful associations with indicators of well-being [27,109].
